# Effect of Community-Based Kangaroo Mother Care Package on Neonatal Mortality Among Preterm and Low Birthweight Infants in Rural Pakistan: Protocol for a Cluster Randomized Controlled Trial

**DOI:** 10.2196/28156

**Published:** 2021-08-10

**Keywords:** community kangaroo mother care, low birth weight, KMC champions, neonatal mortality, RCT protocol, Pakistan

## Abstract

**Background:**

Neonatal mortality due to preterm birth and low birthweight remains a significant challenge in Pakistan. Kangaroo mother care (KMC) is a unique, low-cost intervention proven to reduce neonatal mortality and morbidity and increase exclusive breastfeeding rates. However, KMC has not been attempted in community settings in Pakistan. We aim to implement and evaluate the effectiveness of a community-based KMC package to reduce neonatal morbidity and mortality among preterm and low birthweight (LBW) infants, which will provide evidence for policy development and the large-scale implementation of KMC across the country.

**Objective:**

The primary objective of this trial is to reduce neonatal mortality among preterm and LBW infants. The secondary objectives are growth (measured as weight gain), reduced incidence of possible serious bacterial infection, and increased exclusive breastfeeding and continued breastfeeding practices.

**Methods:**

We designed a community-based cluster randomized controlled trial in one rural district of Pakistan. Stable, LBW babies (weighing 1200 grams to 2500 grams) are included in the study. The community KMC package, consisting of the KMC kit, information and counseling material, and community mobilization through KMC champions (village volunteers), was designed after preliminary research in the same geographical location and implemented in intervention clusters. The standard essential newborn care is offered in the control clusters. Infants are recruited and followed up by independent teams of data collectors. Data are collected on the duration of skin-to-skin contact, growth, breastfeeding practices, morbidities, neonatal mortality, and neurodevelopment status. Data analysis will be conducted based on the intention to treat principle. The Cox regression model will be used to assess the primary outcome of neonatal mortality. The secondary outcomes will be evaluated using linear or logistic regression.

**Results:**

The Ethics Review Committee of Aga Khan University, Pakistan, approved the study protocol in February 2017. Data collection began in August 2019 and will be completed in December 2021. Data analyses are yet to be completed.

**Conclusions:**

This intervention may be effective in preventing sepsis and subsequently improve survival in LBW newborns in Pakistan and other low-income and middle-income countries worldwide.

**Trial Registration:**

clinicaltrials.gov NCT03545204; https://clinicaltrials.gov/ct2/show/NCT03545204

**International Registered Report Identifier (IRRID):**

DERR1-10.2196/28156

## Introduction

Neonatal mortality has emerged as a unique challenge for Pakistan. Although Pakistan has made progress in reducing infant and below 5 years mortality, little progress has been made to improve neonatal mortality in the last 3 decades [1-3]. The primary causes of neonatal mortality in Pakistan are birth asphyxia, sepsis, and preterm births [1,2]. Most neonatal deaths, especially those attributed to preterm births and low birthweight (LBW), can be averted by better coverage and low-cost, evidence-based interventions [4-7]. However, despite these interventions' availability and proven effectiveness, they have not been implemented on a large scale in Pakistan [8,9].

Kangaroo mother care (KMC) is a unique and low-cost intervention that significantly impacts preterm or LBW neonatal outcomes [10]. KMC was first initiated in 1978 by [name] in Bogotá, Colombia, who developed a technologically simple method defined as “early, continuous, and prolonged mother-infant skin-to-skin contact, with (ideally) exclusive breastfeeding.” UNICEF (The United Nations International Children’s Emergency Fund) reported this practice worldwide in 1983, and it was the first time the term “kangaroo’” was used to describe this practice [11]. In 2003, the WHO (World Health Organization) developed the first guidelines on the key aspects of KMC (kangaroo position, kangaroo feeding and nutrition strategy, and early discharge and strict ambulatory follow-up of KMC) [10].

Several studies have demonstrated the benefits of KMC in reducing neonatal morbidity and mortality and improving weight gain and exclusive breastfeeding rates [12-21]. Similarly, Lassi et al. [22] documented early initiation of breastfeeding, hygienic cord care, and KMC as effective neonatal infant and child mortality reduction interventions.

Despite high rates of home births in rural areas [23,24], KMC has never been tried in Pakistan’s community settings. The noncompliance to KMC practices can be best explained by various cultural factors inherent to religious and indigenous practices [25] in the community, including but are not limited to the covering of the body for modesty [23,26]. In addition, a low facility birth rate and a short post-delivery stay among rural communities are significant obstacles to initiating and sustaining KMC in the health facilities [27-29].

Given the high burden of neonatal deaths and the paucity of evidence on locally acceptable KMC, it must be tested in the community setting to generate the evidence to scale up its implementation across the country further. We propose to test the effectiveness of community KMC (cKMC) in our sociocultural context. A preliminary study was conducted to inform the design of the cKMC package and its implementation strategies. The strategies include delivering the KMC kit to mothers; garnering support for KMC; developing a buddy system to support mothers; establishing KMC champions (volunteers) within the communities; mobilizing communities using information, education, and communication (IEC) tools, including video messages and docudramas; and training community health workers on KMC and essential newborn care.

Based on these interventions, we aim to implement a cKMC package to reduce neonatal morbidity and mortality among premature and LBW infants. The primary objective of this trial study is to evaluate the effectiveness of cKMC in lowering neonatal mortality among premature and LBW infants. The secondary objectives include assessing the impact of cKMC on growth (measured as weight gain), the incidence of possible serious bacterial infection (PSBI) and referrals to the hospital, exclusive breastfeeding and continued breastfeeding practices, and neurodevelopmental assessments in a subset of recruited LBW babies at 6 and 12 months of age.

## Methods

### Study Design

We are conducting a cluster randomized controlled trial in one of the rural districts of Pakistan. The cKMC package has been developed based on preliminary research, involving in-depth interviews and focused group discussions with major stakeholders. A conceptual framework was developed based on the existing data to guide research themes (Figure 1).

**Figure 1 figure1:**
[figure not shown]
Conceptual framework and major themes from formative preliminary research. KMC- kangaroo mother care; LBW- low birth weight newborn.

### Study Site

The study is being conducted in 2 subdistricts (Taluka-Johi and Taluka-Khairpur Nathan Shah) of the district Dadu, which is a rural agrarian district in Sindh province of Pakistan. The overall population of the 2 talukas is about 2 million people residing in 54 union councils. The union council is the smallest administrative unit in Pakistan, with 15,000 to 25,000 people. The study area's population is largely poor, with 68% of households belonging to the lowest wealth quintiles. The study area also has an LBW prevalence of 27.7%, with an exclusive breastfeeding rate of 17.3%. Half of the women still deliver at home, and the proportion of facility births is 48.8% [30].

The public sector primarily provides the health care in the target area. There are 2 secondary care hospitals in the study area. There is a basic health unit (BHU) in each union council, and 15 to 20 lady health workers (LHW) are affiliated with each BHU, serving as frontline health care providers for a population of 1000 people in their respective areas.

### Study Population

#### Inclusion and Exclusion Criteria

All stable LBW newborns weighing 1200 grams to 2500 grams are screened within a 72-hour window, followed by enrollment after informed consent to participate in the trial is obtained. Newborns tolerating oral feeding with no respiratory distress, the absence of any symptoms of disease, and the absence of congenital anomalies are included in the study.

Whereas newborns weighing less than 1200 grams and with symptoms of disease according to predefined criteria (ie, unable to tolerate oral feeding; severe respiratory distress, including respiratory rates of less than 20 breaths per minute or more than 60 breaths per minute; grunting–central cyanosis; severe chest in-drawing; convulsions; unconsciousness; severe hypothermia of less than 32°C; apnea; and congenital malformation) are excluded and referred to the nearest health facility for management.

#### Sample Size

We considered union councils in the talukas as the clusters for our trial. The union council comprised a population of 25,000, with expected 29 births per 1000 people. We anticipated 200 LBW births per cluster, given the 27.7% prevalence of LBW in the study area [30]. Literature suggests 13.3% of the LBW infants die in the neonatal stage [31]. With an expected 30% reduction in mortality, 12 clusters (union councils) were needed per arm (a total of 24 clusters for the trial) to achieve 90% power and a 5% significance level. We estimated 200 births with a birth weight of less than 2.5 kg per cluster. A total of 4800 participants in the intervention and control groups are required to complete the study.

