### Outcome Ascertainment

The data are collected in a structured electronic format to ascertain outcomes. The anthropometric measurements are done per standard anthropometry guidelines [33] by the pair of measurers (weight and length). Infant weight is measured on pan scales (model 354; Seca) and length is measured by the infantometer (model 417; Seca). The details of the outcome measures are described in Textbox 1.

Outcome measures and definitions. LBW: low birthweight; PSBI: possible serious bacterial infection; EBF: exclusive breastfeeding defined as the percentage of infants aged 0 to 6 months who are exclusively breastfed; KMC: kangaroo mother care.**Reduction in neonatal mortality:** the reduction of mortality in LBW newborns during the first 28 days of life.**Improvement in growth (nutrition status):** the increase in newborn weight gain from birth and at days 14, 28, 59, 120, 180, and 365; and the increase in the length of the newborn from birth and at days 180 and 365.**Reduction in PSBI incidence:** the reduction in PSBI incidence during the neonatal period (days 14 and 28) and 59 days of life.**Improved EBF:** increase in the EBF rate up to 50% at 6 months of age.**Improved neurodevelopment:** KMC improves neurodevelopment outcomes while impairments in physical growth and brain and central nervous system development can result in cognitive, language, motor, neurosensory impairments, and behavioral disorders. Hence assessment will be done at 12 months of age.

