### Data Analysis

For data analysis, we will use the intention to treat approach using STATA software (version 17; StataCorp). Data will first be analyzed using person-time as the denominator for the primary outcome (neonatal mortality between enrollment and 28 days of age). Hazard ratios and 95% CIs will then be calculated using a Cox regression model to evaluate the effect of the intervention (cKMC) on infant deaths. We will also estimate the impact of cKMC using the number of enrolled infants as the denominator to deduce risk ratios using generalized linear models of the binomial family with a log link function. The summary data for background characteristics in the intervention and control groups will be presented as means and proportions.

The effect of KMC on secondary outcomes (ie, exclusive breastfeeding, weight and length gain, the incidence of illnesses and hospitalizations, and care-seeking behavior) will be assessed using linear or logistic regression after adjusting for clustering in the case of twins or another enrolled baby subsequently born to the same mother, as well as other potential confounders.

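### The 90% power uses a 13.3% death risk stated for LBW infants in general, while the primary analysis counts only deaths after enrolment in stable infants of at least 1200 g, so the stated power is probably too high

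*Protocol article*

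**What the plan says.** The Sample Size section takes its control risk from published work: "Literature suggests 13.3% of the LBW infants die in the neonatal stage". It sets no limit on weight, health or age at entry. It continues: "With an expected 30% reduction in mortality, 12 clusters (union councils) were needed per arm", "to achieve 90% power and a 5% significance level". The cluster size is the count of all low-weight births: "We estimated 200 births with a birth weight of less than 2.5 kg per cluster". With "a total of 24 clusters for the trial", this gives 4800 participants.

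The enrolled population is narrower. Under Inclusion and Exclusion Criteria, infants below 1200 g are excluded, and: "Newborns tolerating oral feeding with no respiratory distress, the absence of any symptoms of disease, and the absence of congenital anomalies are included". Screening, Recruitment, and Intervention Delivery puts the household visit within 72 hours of delivery.

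The Data Analysis section defines the primary outcome as "neonatal mortality between enrollment and 28 days of age", with person-time or the number of enrolled infants as denominator. Textbox 1, under Outcome Ascertainment, words it more loosely: "the reduction of mortality in LBW newborns during the first 28 days of life".

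**The concern.** The planning risk and the analysed risk refer to different sets of deaths. Three groups of deaths that a neonatal risk for LBW infants would include cannot enter the primary analysis:

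- deaths before the recruitment visit;
- deaths of infants under 1200 g;
- deaths of infants already ill or malformed at screening.

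If 13.3% is right for LBW infants as stated, the control risk among enrolled infants is lower. With the relative reduction held at 30%, a lower control risk means fewer deaths and less power. The Sample Size section presents 12 clusters per arm as the number needed, so the plan claims little spare capacity. What is at stake is how a null or imprecise result is read: a trial reported as having 90% power invites the conclusion that a 30% benefit was ruled out.

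**Working it through.** **Inputs from the article.** Control risk 13.3%; 30% reduction, so 0.7 × 13.3% = 9.31%; 12 clusters per arm; 200 infants per cluster; 90% power; 5% significance, taken here as two-sided.

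**Not given in the article.** The intracluster correlation (ICC) or between-cluster coefficient of variation (k), and the mortality after enrolment. The first is solved from the plan's own 90%. The second is an assumed range.

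**Step 1: the plan's own figures.** 25,000 × 0.029 × 0.277 = 201 LBW births per cluster, and 24 × 200 = 4800. Both agree with the article. Without clustering, 13.3% versus 9.31% needs 1322 infants per arm, so 12 × 200 = 2400 implies an allowance for clustering.

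- *Design-effect method.* 2400 / 1322 = 1.815. From 1 + 199 × ICC = 1.815, ICC = 0.0041.
- *k method.* Clusters per arm = 1 + (1.96 + 1.28)² × [p1(1−p1)/m + p2(1−p2)/m + k²(p1² + p2²)] / (p1−p2)². At 13.3% this is 1 + 10.507 × [0.000577 + 0.000422 + 0.02636 k²] / 0.001592. Exactly 12 clusters gives k = 0.159. Exactly 11 gives k = 0.140. Any k between these rounds up to 12.

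The 90% is therefore attainable at 13.3%, but it cannot be reproduced from stated inputs alone.

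**Step 2: worked example at a control risk of 10% (7% with the intervention).**

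- *Design effect.* Effective size is 1322 per arm. Standard errors are √(2 × 0.085 × 0.915 / 1322) = 0.01085 under the null and √((0.0900 + 0.0651) / 1322) = 0.01083 under the alternative. (0.03 − 1.96 × 0.01085) / 0.01083 = 0.81, so power is 79%.
- *k = 0.159.* Variance is 0.000450 + 0.000326 + 0.000378 = 0.001153. √(11 × 0.0009 / 0.001153) − 1.96 = 0.97, so power is 83%.
- *k = 0.140.* Variance is 0.001068, the same expression gives 1.08, and power is 86%.

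**Step 3: power for a 30% reduction, by assumed control risk.**

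| Control risk | ICC 0.0041 | k = 0.159 | k = 0.140 |
|---|---|---|---|
| 13.3% | 90.0% | 90.0% | 92.5% |
| 12% | 86.4% | 87.9% | 90.5% |
| 10% | 79.0% | 83.4% | 86.1% |
| 8% | 68.9% | 76.8% | 79.4% |
| 5% | 48.1% | 60.4% | 62.3% |

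At k = 0.140, power stays at or above 90% down to a control risk of about 11.7%.

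**Step 4: reduction detectable with 90% power at 4800 infants**, with the variation calibrated to exactly 90% at 13.3% (k fixed to ICC fixed): 33-35% at a control risk of 10%, 35-39% at 8% and 42-48% at 5%.

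**Step 5: how far the risk might fall.** If a share S of the deaths precedes enrolment, the risk among those still alive is 0.133(1−S) / (1−0.133S). S = 10% gives 12.1%, 14% gives 11.7% and 20% gives 10.9%. These shares are assumptions with no source in the article, and they leave out the weight and illness exclusions.

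**The case against.** The strongest reply is that no loss of power has been measured. The article gives no mortality after enrolment, the cited source cannot be seen, and 13.3% may not be the true risk for LBW infants in these union councils. The 72 hours is an upper limit, and pregnancy surveillance and birth notification could bring most visits earlier. This stands as to size. It does not remove the mismatch or its direction on the plan's own figure.

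A reader might infer that the design has no slack, because one value of the ICC or k gives exactly 90%. That goes too far. Clusters come in whole numbers, and k as low as about 0.14 also leads to 12. On that reading a fall from 13.3% to about 11.7% still leaves 90%.

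A reader might also infer that Textbox 1 and the Data Analysis section define two different primary endpoints. For an enrolled infant, every death in the first 28 days of life falls after enrolment, so among enrolled infants the two wordings count the same deaths. The analysis section settles the window and the denominator. What remains is loose wording.

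The absence of an ICC or k is not part of this point, since a condensed article commonly leaves it to the full protocol. Finally, the planned 95% confidence intervals would show imprecision whatever the stated power, which limits the harm.

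**Conclusion.** The point holds in a limited form. The planning risk is stated for LBW infants in general, while the analysed risk is that of stable, eligible infants from enrolment to day 28, with no stated adjustment. Unless 13.3% already describes such infants, which the Sample Size section does not say, the 90% is too favourable.

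The size is conditional: about 86-90% power at a control risk of 12%, 79-86% at 10%, 69-79% at 8% and 48-62% at 5%. These figures assume a two-sided 5% test, 200 enrolled infants in each cluster, a 30% relative reduction that applies unchanged to deaths after enrolment, and between-cluster variation as implied by the stated 90%.

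It would be tempting to conclude that the trial does not deliver its power. The article does not support that as fact, because neither the post-enrolment risk nor the between-cluster variation is given. The point concerns a planning assumption. The estimand, bias and type I error are unaffected, and it is a worthwhile correction rather than a critical one.

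**What to change.** Restate the planning control risk as death from enrolment to day 28 in infants who meet the eligibility criteria. Possible sources, in order:

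- the baseline survey, which collected neonatal mortality, if its data can be restricted to such infants and to that window (the article does not show that they can);
- the pooled arm-blinded death rate in the trial, with the assumed effect stated, because a pooled rate alone does not give a control risk. With equal arms and a 30% reduction, control risk = pooled rate / 0.85, so a pooled 8.5% would mean 10%;
- otherwise, an explicit range.

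Then restate the power for a 30% reduction and the reduction detectable with 90% power at 4800 infants. As a minor edit, give Textbox 1 the same outcome window as the Data Analysis section.

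This costs a few restated figures and one sentence. It needs no extra enrolment and leaves the analysis unchanged. The only downside is a less favourable stated power.

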#### Randomization

The 2 targeted talukas have a total of 54 union councils. Out of these, 24 were randomly selected by an independent researcher using a computer-generated program (Figure 2).

**Figure 2 figure2:**
[figure not shown]
Study site and selected clusters. UC: union councils.

The clusters (union councils) were randomized using a restricted randomization scheme using the following indicators: population, live birth, the prevalence of LBW, neonatal mortality, skin-to-skin contact, breastfeeding practices, and distance from the taluka hospital. We conducted a baseline survey of the study area to collect data on these indicators. Blinding is not possible because of the nature of the intervention; however, to minimize measurement bias on the effect of the intervention, the data collection team is independent of the implementation team.

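### The mortality models are stated without the council indicators that restricted the randomisation; once clustering is handled, the test is conservative and the interval somewhat too wide if those indicators predict mortality

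*Protocol article*

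**What the plan says.** **Design.** Methods, Randomization: "The clusters (union councils) were randomized using a restricted randomization scheme using the following indicators". The list is "population, live birth, the prevalence of LBW, neonatal mortality, skin-to-skin contact, breastfeeding practices, and distance from the taluka hospital". The values were in hand before allocation: "We conducted a baseline survey of the study area to collect data on these indicators".

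**Primary analysis.** Methods, Data Analysis: "Hazard ratios and 95% CIs will then be calculated using a Cox regression model to evaluate the effect of the intervention (cKMC) on infant deaths". The same outcome is also analysed per enrolled infant, "to deduce risk ratios using generalized linear models of the binomial family with a log link function". Neither sentence names a covariate or a union-council term.

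**Secondary analysis.** The next paragraph provides for "adjusting for clustering in the case of twins or another enrolled baby subsequently born to the same mother, as well as other potential confounders". That adjustment is attached to the secondary outcomes only.

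**Enrolment weight.** Weight enters through eligibility: "All stable LBW newborns weighing 1200 grams to 2500 grams are screened within a 72-hour window". It is not among the restriction indicators.

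**The concern.** Restriction makes the arms more alike on the chosen indicators than simple randomisation would. If those indicators predict neonatal death, the treatment contrast varies less between possible allocations. A council-level analysis that leaves them out still counts their variation as error, so it reports a standard error for a less balanced design than the one used. The test is then conservative and the interval too wide. With 24 union councils, between-council variation accounts for much of the variance, so this can matter.

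The article does discuss covariate adjustment, but attaches it to the secondary outcomes and not to the primary one. A reader is likely to take the mortality models as unadjusted.

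A second, separate point concerns enrolment weight. Infants are recruited after councils are allocated, without blinding, and pregnant women are counselled differently by arm. The enrolled groups could therefore differ in weight, which restriction on council-level indicators need not prevent.

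**Working it through.** **Inputs from the article (Sample Size):** 13.3% control mortality; 30% reduction, so 0.133 × 0.7 = 0.0931; 200 infants per council; 12 councils per arm; 90% power; 5% significance (taken as two-sided).

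**Assumed, because the article gives neither:** the between-council coefficient of variation k, and the share R² of between-council variance that the indicators explain. The acceptance rule for the restriction is also assumed.

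**1. The plan's own figure.** Councils per arm by the Hayes–Bennett formula:

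c = 1 + (1.96 + 1.2816)² × [B + k²S] / d²

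- B = (0.133 × 0.867 + 0.0931 × 0.9069)/200 = 0.000999
- S = 0.133² + 0.0931² = 0.02636
- d² = (0.133 − 0.0931)² = 0.001592

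At k = 0.15: c = 1 + 10.507 × (0.000999 + 0.000593)/0.001592 = 11.5, which rounds up to 12. Exactly 12 is reached at k ≈ 0.159. The stated size therefore fits k of about 0.15 to 0.16, but that value is back-solved, not stated.

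**2. Why the omission makes the test conservative.** On the log-rate scale, one control-type council has sampling variance 0.867/(200 × 0.133) = 0.0326 and between-council variance k². The share of total variance that the indicators explain is R² × k²/(k² + 0.0326). If restriction balances the indicators almost completely, the true standard error is the reported one times √(1 − share). The unadjusted test, with critical value 2.07 on 22 degrees of freedom, then acts as if that value were 2.07/√(1 − share).

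| k | R² | share | SE factor | effective critical value | type I error |
|---|---|---|---|---|---|
| 0.15 | 0.3 | 0.12 | 0.94 | 2.21 | 3.8% |
| 0.15 | 0.6 | 0.24 | 0.87 | 2.39 | 2.6% |
| 0.25 | 0.3 | 0.20 | 0.90 | 2.31 | 3.0% |
| 0.25 | 0.6 | 0.39 | 0.78 | 2.67 | 1.4% |

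**3. Simulation.** 24 councils of 200 infants, restricted allocation, council-level analysis with and without the restriction covariate, 3,000 trials per setting:

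| k | R² | type I, unadjusted | type I, adjusted | power, unadjusted | power, adjusted |
|---|---|---|---|---|---|
| 0.15 | 0 | 4.8% | 5.0% | 0.905 | 0.904 |
| 0.15 | 0.3 | 3.6% | 4.6% | 0.914 | 0.932 |
| 0.15 | 0.6 | 2.8% | 5.4% | 0.932 | 0.963 |
| 0.25 | 0 | 4.7% | 4.9% | 0.725 | 0.727 |
| 0.25 | 0.3 | 3.6% | 5.6% | 0.739 | 0.798 |
| 0.25 | 0.6 | 1.4% | 5.2% | 0.761 | 0.895 |

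This agrees with step 2. The adjusted interval is about 0 to 13% narrower at k = 0.15 and about 0 to 20% narrower at k = 0.25. A variant with three indicators and the best 10% of 200 allocations gave unadjusted type I error of 4.5% and 2.8% at k = 0.16, and 2.7% and 2.5% at k = 0.25, for R² of 25% and 50%.

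**4. Closed-form gain, as a check.** Replacing k² by k²(1 − R²) in step 1 gives power of 0.90, 0.93 and 0.95 at k = 0.159, and 0.73, 0.80 and 0.87 at k = 0.25, for R² of 0, 25% and 50%. This overstates the net gain: it charges no degrees of freedom, and its R² = 0 reference ignores the small rise in unadjusted power under restriction (0.905 to 0.932 at k = 0.15 in step 3).

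**5. The opposite error in the models as written.** Without clustering, 1,322 infants per arm would suffice, so 2,400 implies a design effect of 2400/1322 = 1.82 and an intracluster correlation of 0.82/199 = 0.0041. An analysis with no cluster term has an interval too narrow by √1.82 = 1.35 and type I error of about 15%.

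**The case against.** **The article is silent rather than committed.** It never calls the primary analysis unadjusted, and a covariate list is commonly left to an analysis plan, which is not shown here. This stands: one cannot say that the trial has decided to ignore the indicators. The point survives because the article does assign adjustment, and assigns it only to the secondary outcomes.

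**A reader might infer that the precision bought by restriction is lost.** It is not. Restriction lowers the true variance whether or not the model adjusts. What is missed is its reflection in the standard error, and only if the indicators are prognostic.

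**A reader might infer that the primary interval, as written, is too wide.** The documents do not support that. With no union-council term named, the larger risk is an interval that is too narrow. The present point applies once that is corrected.

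**Enrolment weight is not part of the restriction argument.** Correct. Leaving it out cannot waste balance that was never imposed on it. It stands on recruitment after unblinded allocation, and the documents give no figure for its prognostic strength.

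**The size is assumed, and no shortfall against the plan is shown.** This also stands. At k ≈ 0.16 the unadjusted analysis already has the planned 90% power. The larger gains need k = 0.25, and the most conservative type I errors need strongly prognostic indicators; the documents state neither.

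**Adjusting for two or three of seven leaves the rest in the error term.** True, but entering all seven cuts the degrees of freedom from 22 to 15 (critical value 2.07 to 2.13). A short list is the usual compromise.

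**Conclusion.** The point holds as a moderate, inexpensive improvement to the primary analysis. The design uses seven council indicators that the stated mortality models do not use. Given a valid cluster method, omitting prognostic indicators errs on the conservative side: it does not create false positives, but it costs power and widens the interval.

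Under the assumed values, unadjusted type I error is about 3% to 5% at k = 0.15, and falls to about 1.4% to 2.5% at k = 0.25 with strongly prognostic indicators. For R² of 30% to 60%, the power gain from adjustment is about 2 to 3 points at k = 0.15 (0.914 to 0.932, and 0.932 to 0.963) and about 6 to 13 points at k = 0.25 (0.739 to 0.798, and 0.761 to 0.895). With non-prognostic indicators the gain is nil. These figures depend on k, R² and an acceptance rule that the article does not report. They should be read as a range, with the lower end closer to the planning assumptions.

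**What to change.** Before analysis, and together with a method that accounts for the union council, prespecify that the primary Cox and risk-ratio models:

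- adjust for two or three restriction indicators expected to be most prognostic, for example baseline neonatal mortality, LBW prevalence and distance to the taluka hospital, each as the council's baseline-survey value;
- adjust, for the separate reason given above, for each infant's weight at enrolment;
- are accompanied by the unadjusted estimate as supportive;
- base any permutation test on the same restricted set of allocations from which the actual one was drawn.

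**Cost.** The change is to wording: the council values come from the completed survey, and weight is needed for eligibility. Two or three of the 22 council-level degrees of freedom are spent, leaving 20 or 19. The adjusted hazard ratio is a conditional quantity and will not coincide exactly with the unadjusted one. The adjusted log-binomial model may fail to converge, so a fallback estimator for the risk ratio should be named in advance. Because enrolment may fall up to 72 hours after birth and counselling starts in pregnancy, the plan should say which recorded weight is used.
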